#### Effectiveness (primary intervention outcome)

The effectiveness of the helpline service will be evaluated at both an individual participant and population (health district) level.

Participant-level effectiveness will be evaluated using a pre–post cohort study. The primary outcome to assess individual effectiveness will be self-reported healthcare use (eg, general practitioner and imaging usage). This will be compared between an independent cohort of participants with a primary complaint of LBP who use the original service, and an independent cohort who use the upgraded service. The primary outcome will be analysed 3 months post service initiation. Cohort participant questionnaires will also capture secondary outcomes including pain intensity,^50^ disability,^51^ quality of life,^52^ the validated single-item physical activity question,^53^ two-item pain self-efficacy,^54^ health confidence score^55^ and acceptability.^41^ Based on historical service volume data from the MHA helpline, we anticipate approximately 50 participants in the preupgrade period and will require a minimum of 208 participants in the postupgrade period to detect an event rate difference of 4 healthcare service utilisations between the preupgrade and postupgrade cohort, with 80% power and 5% type-1 error rate. This is the equivalent of a 40% difference based on an average health service utilisation rate of 10 services per participant over 12 months observed in unpublished work.^56^ Adjusting for a loss to follow-up of 15% in the postupgrade cohort, we will require 245 participants postupgrade to achieve the required 208 completers. Combined with the anticipated preupgrade cohort, the total sample size is 295 participants.

Population effectiveness will be evaluated using aggregated Local Health District data on ED presentations for patients with a complaint of LBP. The analyses will be restricted to the Mid North Coast Local Health District (or relevant hospitals) data corresponding with the location of the media campaign. An interrupted time series design will be used to analyse the monthly change in LBP presentation rates and any associated trend change following the introduction of the media campaign.

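### The 15% loss to follow-up is applied to the postupgrade cohort only; if it also applies to the preupgrade cohort, power for the primary outcome is about 74–75%, not 80%

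*Protocol article*

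**What the plan says.** All the figures are in the Effectiveness (primary intervention outcome) section of the protocol article.

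- **Preupgrade cohort:** "we anticipate approximately 50 participants in the preupgrade period". The figure is based on historical helpline volume.
- **Postupgrade cohort:** the study "will require a minimum of 208 participants in the postupgrade period".
- **Effect:** the purpose is "to detect an event rate difference of 4 healthcare service utilisations", set against an "average health service utilisation rate of 10 services per participant over 12 months" and described as a 40% difference.
- **Error rates:** "with 80% power and 5% type-1 error rate". Sidedness is not stated for this calculation.
- **Loss to follow-up:** "Adjusting for a loss to follow-up of 15% in the postupgrade cohort, we will require 245 participants postupgrade to achieve the required 208 completers". The preupgrade cohort is then added, for a total of 295.

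Two other sections bear on retention. Pre–post cohort study participants (from the helpline) describes one recruitment and consent route, with invitations to baseline, 3-month and 6-month questionnaires, for both cohorts. Participant-level data gives a single questionnaire schedule and does not distinguish the periods. The Data analysis section specifies negative binomial regression with a rate ratio of postupgrade to preupgrade.

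**The concern.** The calculation mixes two scales. In the postupgrade cohort, 208 is a completer count and 245 an enrolment count. In the preupgrade cohort, the same 50 is used in the power calculation, where it acts as a completer count, and in the total of 295, where it is added to an enrolment count. Both uses are right only if no preupgrade participant is lost by 3 months.

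Nothing in the article supports that. The follow-up procedures are the same. The Introduction describes the existing service as one-off support and says the upgraded service will add follow-up support, so there is no evident reason to expect better retention before the upgrade.

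The preupgrade cohort is also the small one and contributes most of the variance of the comparison. The allowance for loss is therefore made where loss costs little and left out where it costs most. At stake is whether the power claimed for the primary intervention outcome is what the planned enrolment delivers.

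**Working it through.** **1. The plan's own figures.** 208/0.85 = 244.7, rounded up to 245. 245 + 50 = 295. Both reproduce exactly.

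**2. Which scale the 50 is on.** It is added to 245 (enrolled), not to 208 (completers), and it comes from service volume. Had it been a completer count at 15% loss, enrolment would be 50/0.85 = 58.8, so 59, and the total 245 + 59 = 304. The stated 295 fits an enrolment count.

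**3. Preupgrade completers at the plan's own loss rate.** 50 × 0.85 = 42.5, so 42 or 43.

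**4. Power model.** The 208 cannot be reproduced independently because no dispersion is given. I used a Wald test of the log rate ratio under a negative binomial model:

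V = (1/m₀ + k)/n₀ + (1/m₁ + k)/n₁, power = Φ(|ln(m₁/m₀)|/√V − 1.96)

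Here n₀ and n₁ are preupgrade and postupgrade completers, m₀ and m₁ the mean counts, and k the dispersion. Assumptions: a two-sided 5% test, and a reduction from 10 to 6 services (ratio 0.6, ln 0.6 = −0.5108). I chose k so that 50 versus 208 gives exactly the plan's 80%, then changed n₀ alone. For 80% power, V must equal (0.5108/2.8016)² = 0.03325.

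- *12-month means, 10 v 6:* k = 1.227. At 50 v 208, V = 1.3272/50 + 1.3939/208 = 0.02654 + 0.00670 = 0.03325. The preupgrade share is 0.02654/0.03325 = 80%.
- *3-month means, 2.5 v 1.5, with k recalibrated:* k = 0.888. V = 0.02577 + 0.00748 = 0.03325. The preupgrade share is 78%.

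**5. Replace 50 by 42.5.** On the 12-month scale V = 1.3272/42.5 + 0.00670 = 0.03793 and √V = 0.1948. Then 0.5108/0.1948 = 2.623, and power = Φ(2.623 − 1.96) = 74.6%. The 3-month calibration gives 74.8%.

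| Preupgrade loss | Completers | Power, 12-month calibration | Power, 3-month calibration |
|---|---|---|---|
| 0% (as planned) | 50 | 80.0% | 80.0% |
| 5% | 47.5 | 78.4% | 78.4% |
| 10% | 45 | 76.6% | 76.7% |
| 15% | 43 | 75.0% | 75.2% |
| 15% | 42 | 74.2% | 74.4% |

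**6. Robustness.** A comparison of means with a back-solved SD of 9.06 gives 75.0% (43) and 74.2% (42). With one-sided tests the results are about 75–76%. Pooled-null variances, 6-month means, or an increase instead of a decrease leave the shortfall at about 4 to 6 points.

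**7. Detectable effect.** With 42.5 v 208 completers, 80% power is reached at a rate ratio of about 0.58 on either calibration, against the planned 0.60.

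**8. Can the postupgrade cohort compensate?** Only poorly. If all 245 completed, power with 42.5 preupgrade completers would be about 76%. Restoring 80% would take roughly 470 to 850 postupgrade completers, depending on the calibration and on whether 42 or 43 complete.

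**The case against.** **The sums are right.** They are. Both 245 and 295 reproduce, so this is an unstated and optimistic assumption about preupgrade retention, not a slip in arithmetic.

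**The shortfall is conditional.** This also stands. The 15% is given expressly for the postupgrade cohort, and no preupgrade rate appears anywhere. At 5% loss the effect is under 2 points. The 50 is itself approximate, and ordinary variation in recruitment could be as large as the adjustment. None of this supports zero loss, but the power must be stated as what follows if the plan's 15% is carried across.

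**It is small beside the design's other limits.** This is a non-randomised pre–post comparison whose causal limits the article acknowledges. A loss of about 5 points leaves the model and the comparison unchanged, which argues for a moderate rating, not for leaving the claim as it is.

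**Stronger readings that a reader might infer.**
- *That power is nearer 65%.* Keeping k = 1.227 and moving the effect to 3-month counts gives 65.0% with 42.5 preupgrade completers. But the same move gives 70.6% with all 50 completing, so much of that drop comes from the time scale of the effect size, a separate question. The one-sided loss adjustment accounts for about 5 to 6 points. A detectable ratio well below 0.58 mixes the two issues in the same way.
- *That one definite postupgrade number would repair the power.* The required number moves by hundreds with the dispersion, which the article does not give.
- *That the shortfall cannot be recovered, or that more enrolment is ruled out.* Recruiting 59 preupgrade participants would keep 50 completers. Whether call volume allows it cannot be judged from the article.

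**Conclusion.** The point holds, at moderate weight. As written, the calculation assumes complete preupgrade follow-up without giving a reason, while allowing 15% loss in a cohort followed in the same way. Carrying the plan's own 15% across leaves 42–43 preupgrade completers and power of about 74–75% for the stated effect, instead of 80%.

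This rests on two assumptions: that preupgrade loss resembles postupgrade loss, and that the unstated dispersion is whatever makes 50 versus 208 give 80%. The first drives the size of the shortfall (about 77% power at 10% loss, 78% at 5%). The second hardly matters, because the two-sided forms tried agree to within about a point. The planned analysis itself is not put in doubt.

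**What to change.** Apply the loss to both cohorts and restate the calculation: 50 + 245 enrolled, about 42 + 208 completers, power about 75% for a rate ratio of 0.60, or a detectable rate ratio of about 0.58 at 80% power. State the dispersion and sidedness used, so that the restated figure can be checked. If the team has grounds to expect no preupgrade loss, give them instead.

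The cost is one or two sentences and a slightly less favourable stated power. Enrolment need not change. If preupgrade call volume allows, recruiting 59 (59 × 0.85 = 50.15 completers, total 304) would keep the 80%, but that is optional.

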#### Adoption

Adoption of the helpline will evaluate the equitable use of the service by examining user representation across different patient demographics. This will be assessed using monthly number of unscheduled callers with a primary complaint of LBP across different demographics (eg, age, sex, rurality—determined using participants’ postcode). An interrupted time series design stratifying by participant demographic will be used to analyse this. Quantitative results will be complemented by one-on-one qualitative interviews with approximately 15–20 participants (pending data saturation) from the pre–post cohort study. Interviews will be conducted online and are estimated to take between 45 and 60 min. Results will be combined to understand the type of patients using the service as well as potential barriers and facilitators to utilisation. Adoption evaluation will inform changes to the intervention, media campaign or infrastructure that may be needed to improve equitable service access.

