Characteristics of helpline users (eg, different geographical regions and age groups)	(1) Mixed methods	Monthly helpline call numbers Cohort participant interviews	Continuous 18 months pre–post helpline upgrade Pre–post campaign period	LBP monthly call rates stratified by demographic Qualitative study using PRISM framework	Segmented regression with stratification Mixture of inductive and deductive thematic interview analysis	All LBP phone calls/services received 15–20 cohort participants
Implementation						
Fidelity of the upgrade helpline service to fidelity checklist Participants perceived acceptability of the helpline	(1) Process evaluation using mixed methods	(1) Data audit of provided services (2) Cohort self-reported data	Continuous data collection following the upgrade Pre–post cohort	Fidelity checklist TFAQ acceptability questionnaire	Implementation fidelity Descriptive (visual) analysis	20% random audit of all LBP services provided As per effectiveness outcome
Maintenance						
Sustainability of the upgraded helpline service	(1) Mixed methods	Purposive sample for qualitative study Monthly calls in post campaign period and individual effectiveness at 6 months.	Post campaign period for qualitative data (routine data will be continuous) Post campaign	Qualitative study using PRISM framework Proportion of calls post media campaign completion	Mixture of Inductive and deductive interview analysis Segmented regression and negative binomial regression for count of healthcare service utilisation	15–20 cohort participants, 3–10 participants per stakeholder group All LBP phone calls/services

ED, emergency department; LBP, low back pain; PRISM, Practical Robust Implementation Sustainability Model; RE-AIM, Reach, Effectiveness, Adoption, Implementation and Maintenance; TFAQ, Theoretical Framework of Acceptability Questionnaire.

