#### Secondary data

ED population-level data: Deidentified, aggregated data on monthly ED presentations for LBP among patients aged ≥18 years will be obtained from the Mid North Coast Local Health District. Presentations will be identified using the International Classification of Diseases 9th and 10th editions and Systematized Nomenclature of Medicine-Clinical Terminology (SNOMED CT) diagnostic codes adapted from Anderson *et al*^58^ (see online supplemental appendix B). Data will be extracted through the Emergency Department Data Collection via the NSW Centre for Health Record Linkage. Extraction will cover the 18 months before and after the helpline upgrade. Panel data: Deidentified and aggregated population awareness of the helpline will be collected via panel surveys. These will be administered by a panellist provider premedia and postmedia campaign and stored on the University of Sydney’s highly secure SharePoint site. MHA data: Deidentified demographic data routinely collected by MHA, including aggregated information on age, sex, physical activity, pain severity and area of residence, will be compared with demographic data of the cohorts to assess for selection bias.

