### Data analysis

Quantitative data will be analysed to evaluate the reach, effectiveness, adoption and implementation dimensions of the RE-AIM framework. Descriptive statistics will summarise demographics and key characteristics of helpline callers, cohort participants, campaign survey respondents and individuals presenting to the Mid North Coast Local Health District ED with LBP. Descriptive statistics will also be used to summarise the fidelity of the delivered helpline service, with the proportion of total calls rated as poor, average, good or high. Participant-reported acceptability will be summarised visually using stacked horizontal bar charts to display the proportion of respondents selecting each response category across the seven acceptability domains.

A χ² test will be used to compare the postcampaign proportion of individuals aware of the helpline between the control region and the intervention region (exposed to the media campaign). Data collected prior to the campaign will be used to provide a descriptive comparison of baseline awareness between the two regions. If notable baseline differences in awareness are identified, a logistic regression will be conducted to estimate the association between the region (intervention or control) and postcampaign awareness, adjusting for baseline awareness as a covariate. An interrupted time series with segmented regression and a generalised Poisson or negative binomial model (dependent on data overdispersion) will be used to evaluate the impact of the media campaign (eg, the interruption point)^59^ on the monthly helpline call rate, the monthly helpline call rate stratified by age, sex and rurality demographics, and the monthly rate of ED presentations for LBP within the campaign exposed Local Health District. Exploratory analyses will be conducted to inspect visual trends, with adjustments for autocorrelation and seasonality conducted prior to final analysis. The estimated impact of the media campaign on each outcome, for example, an immediate (stepped change) or trend change (slope change) will be prespecified in the statistical analysis plan once the final media strategy has been determined.

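### Adoption aims to judge equitable use through user representation, but the planned analysis estimates only change within each demographic group, so it cannot show that a group is under-represented

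*Protocol article*

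**What the plan says.** The Adoption section of the Protocol article sets the aim: "Adoption of the helpline will evaluate the equitable use of the service by examining user representation across different patient demographics". It then names the measure: "This will be assessed using monthly number of unscheduled callers with a primary complaint of LBP across different demographics". The analysis follows: "An interrupted time series design stratifying by participant demographic will be used to analyse this".

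The adoption row of Table 1 gives the outcome as "LBP monthly call rates stratified by demographic". The Data analysis section specifies "An interrupted time series with segmented regression and a generalised Poisson or negative binomial model" and lists "the monthly helpline call rate stratified by age, sex and rurality demographics" among the series to which it applies, with the media campaign as the interruption. Both places speak of a rate. Neither defines a denominator, and the Adoption section speaks of a monthly number.

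Two other statements bear on who the callers are. The Data analysis section says: "Descriptive statistics will summarise demographics and key characteristics of helpline callers, cohort participants, campaign survey respondents". The Secondary data section says that demographic data routinely held by the helpline operator "will be compared with demographic data of the cohorts to assess for selection bias".

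The Adoption section adds about 15–20 interviews with cohort participants. It says that the results will guide changes to the service, the campaign or the infrastructure, so that access becomes more equitable.

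**The concern.** Representation compares the mix of users with the mix of some reference population. The stated analysis compares each group with its own past. The two answer different questions, and the documents supply no reference population that would link them.

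If the campaign raises calls by the same factor in every group, the stratified results look alike, and a group that was under-served beforehand stays under-served by the same factor. That gap is what an evaluation of equitable use should show, because the Adoption results are meant to guide changes that improve access. With only within-group change reported, an under-represented group can be overlooked.

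**Working it through.** The plan gives no figure for Adoption that could be reproduced: Table 1 lists all LBP calls as the sample, with no power statement or threshold. The check is therefore in three parts.

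**1. What the model estimates.** For group g in month t, with a log link and the campaign starting at t0 (D = 1 from t0 onwards):

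log(expected calls) = a_g + b1·t + b2·D + b3·(t − t0)·D

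The step ratio is exp(b2) and the slope ratio is exp(b3). The size of the group enters neither. If a population offset log(N_g) that is constant over time is added, the intercept becomes a_g − log(N_g), while b2 and b3 are unchanged. The offset alone therefore adds nothing to the campaign effects. Only a comparison of levels between groups carries information on representation, and that needs a denominator.

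**2. Illustration.** The documents give neither caller shares nor population shares by group, so the shares below are assumptions. The volume is taken as 50 over 6 months, about 8.3 per month. It rests on the figure of 50 participants over the 6-month initial implementation trial in the Testing and refinement section, and it cancels from every ratio below. The series has 18 months before and 12 months after the campaign, as in the Reach section. Calls double in every group.

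- Representation ratio = caller share / population share.
- Per-head ratio = (caller share / population share) / ((1 − caller share) / (1 − population share)).

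| Population share of group | Caller share of group | Representation ratio | Per-head ratio, group vs rest | Step ratio, group | Step ratio, rest |
|---|---|---|---|---|---|
| 30% | 30% | 1.00 | 1.00 | 2.00 | 2.00 |
| 30% | 20% | 0.67 | (0.20/0.30)/(0.80/0.70) = 0.58 | 2.00 | 2.00 |
| 30% | 10% | 0.33 | (0.10/0.30)/(0.90/0.70) = 0.26 | 2.00 | 2.00 |
| 50% | 5% | 0.10 | (0.05/0.50)/(0.95/0.50) = 0.05 | 2.00 | 2.00 |

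Seen from the larger group, the second and third rows are a group with 70% of the population and 80% or 90% of calls: (0.80/0.70)/(0.20/0.30) = 1.71 and (0.90/0.70)/(0.10/0.30) = 3.86. The slope ratio is 1.00 throughout. A fully representative service and a strongly unrepresentative one give the same time-series result.

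**3. Whether another part of the plan supplies the reference.**

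- The descriptive summary of callers yields caller shares, which are the numerator of a representation ratio. No comparator is named.
- The comparison in the Secondary data section is between callers and the research cohorts. It tests who enrolled, not who is missing from the helpline.
- The Setting section gives the district's population (230 000) and likens its make-up to the nation's. This describes the setting and is not tied to Adoption.
- The interviewees are cohort participants, all of whom have used the helpline. Groups that do not call are not heard there.

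**The case against.** The strongest objection is that a condensed article need not name a denominator, since offsets and reference populations are ordinary content for a statistical analysis plan. The word rate may imply one, and the planned caller summary already provides the shares. On this view nothing is lost: age, sex and postcode are captured, and a comparison with published counts can be made at any time.

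Much of this stands. The caller summary is planned, so it would be wrong to say that the stratified regression is the only quantitative description of callers. No data are lost. The objection fails on the main point, because the article states both the aim and the analysis, and the analysis cannot answer the aim. For these series, the Data analysis section defers the form of the campaign effect (step or slope) to the analysis plan, and neither form bears on representation.

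A reader might infer that the plan would declare an unrepresentative service equitable. The documents do not support that: they set no rule, threshold or test for equity. Nor do they show that changes would be aimed at the wrong group, since the counts are to be combined with interviews before anything is changed.

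Two further cautions are fair. The helpline is national, while the campaign is primarily in one district, so the area that supplies callers is expected to shift at the interruption. A single denominator would then confuse campaign targeting with equity. Also, population share is only a proxy for need, because LBP may be more common in some groups than in others.

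**Conclusion.** The concern holds in a limited form. The Adoption analysis, as stated, measures change within groups. The descriptive summary has no reference population. The plan therefore cannot detect that a group is under-represented, although that is the aim it sets.

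That the step and slope ratios do not depend on group size follows from the model and rests on no assumed number. The size of any gap that goes unseen is unknown. The 1.7- to 3.9-fold figures, and the per-head range of 0.05 to 0.58, illustrate assumed shares and do not estimate this service. Adoption is a supporting RE-AIM dimension. The primary outcome, its sample size and its analysis are unaffected. The change is worth making because it is cheap and the results are meant to guide decisions on access.

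**What to change.** In the Adoption section, the adoption row of Table 1 and the Data analysis section:

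- Keep the stratified segmented regression and describe it as the analysis of change in caller mix. It needs no population offset.
- Add, for each age, sex and rurality group, a descriptive representation ratio: share of LBP callers divided by share of the adult population, with 95% CI, before and after the campaign.
- Report the ratio separately for Mid North Coast callers against that district's population and for all callers against the national population, so that the regional targeting of the campaign is not read as a change in equity.
- State as a limitation that general population counts only approximate the number of people with LBP in each group.

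The alternative is to restate the Adoption aim as change in caller mix after the campaign and to drop the claim to evaluate equitable use.

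The cost is wording plus published population counts by age, sex and postcode-based rurality. No new participant data are needed. The documents do not say how many callers came from the district before the campaign, so the intervals for that period may be wide.
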